## Abstract

**Background:**

Acupuncture is a method for treating tic disorder. However, there is a lack of sufficient clinical objective basis in regards of its treatment efficacy. Indeed, there are structural abnormalities present in energy metabolism and infrared thermography in children with tic disorder. Therefore, this study proposes a clinical trial scheme to explore the possible mechanism of acupuncture in treating tic disorder.

**Methods:**

This randomized controlled trial will recruit a total of 90 children, in which they will be divided into non-intervention group and intervention group. The non-intervention group consists of 30 healthy children while the intervention group consists of 60 children with tic disorder. The intervention group will be randomly allocated into either the treatment group or the control group, with 30 children randomly assigned in each group. Children either received acupuncture treatment and behavioral therapy (treatment group) or sham acupuncture treatment and behavioral therapy (control group), 3 treatment sessions per week for a period of 12 weeks, with a total of 36 treatment sessions. Outcome measures include YGTSS, urinary and fecal metabolomics, infrared thermography of body surface including governor vessel. For the intervention group, these outcome measures will be collected at the baseline and 90th day prior to intervention. Whereas for the non-intervention group, outcome measures (excluding YGTSS) will be collected at the baseline.

**Discussion:**

The main outcome will be to observe the changes of the severity of tic condition, the secondary outcome will be to observe the changes of structural characteristic of infrared thermography of body surface/acupoints along the governor vessel and to evaluate the changes of urinary and fecal metabolomics at the end of the treatment, so as to analyze the relationship between them and to provide further knowledge in understanding the possible mechanism of acupuncture in improving the clinical symptoms via regulating and restoring the body metabolomics network, which in future it can develop as a set of clinical guideline (diagnosis, treatment, assessment, prognosis) in treating tic disorder. ChiCTR2300075188(Chinese Clinical Trial Registry, http://www.chictr.org.cn, registered on 29 August 2023).

**Supplementary Information:**

The online version contains supplementary material available at 10.1186/s12906-024-04534-x.

## Introduction

Tic disorder (TD) refers to a kind of neuropsychiatric disorder that usually originated in children or young adults. The main clinical features include involuntary, repetitive, sudden, rapid and non-rhythmic movement of one or more parts of the body and may accompanied with vocal twitch [1]. According to foreign research statistics, the prevalence rate of TD in minors aged 5–18 is 0.4–3.8% [2], and the overall prevalence rate is 1%. It has been reported that about 3% of school-age children have history of transient TD, and 80–90% of TD patients have at least one mental disorder [3]. Furthermore, the symptoms of TD can progress into adulthood, which may lead to employment issues or partner/marriage conflict, which seriously affect one’s quality of life. The neuropathological mechanism of TD is still unclear [4]. At present, it is thought that its occurrence may be related to the content of dopamine in substantia nigra, neuroinflammatory reaction and immune reaction etc [5]. Currently, the clinical diagnosis of TD is mainly based on the symptoms itself, and due to lack of specific biomarker, TD is easy to be misdiagnosed, causing children to lose the opportunity to receive treatment in the golden period. In modern western medicine, a combination of behavioral therapy and drug therapy is usually applied to treat patients with TD. The existing first-line drugs in clinical practice normally require patients to consume it for a long period of time, and the long-term efficacy of the drugs is uncertain, moreover there are various side effects present while consuming it such as nausea, vomiting, headache, insomnia, anxiety and irritability etc [2]. .Acupuncture has been proved to be effective in treating TD, however, the pre-clinical diagnosis is mainly based on scale evaluation [6], and there is a lack of objective evaluation indicators and detection methods.

Energy metabolism may play an important breakthrough in patients with TD. Studies have found that there are differences in neurotransmitters in urine between children with TD and healthy children. Animal models of TD were presented with neurotransmitter abnormalities in cerebrospinal fluid (CSF), detection of neurotransmitters in urine, response to drug therapy that blocks or stimulates neurotransmitters, autopsy findings and neuroimaging studies, which mainly involving dopaminergic, glutamatergic and 5- hydroxytryptamine neurotransmitters [7, 8]. The brain-gut axis is closely related to the occurrence of neuropsychiatric diseases [9]. TD is a chronic neurological disorder. After various clinical observation and animal experiments, the changes of intestinal microflora in patients with TD seem to be specific [10]. The methods of utilizing probiotics and fecal microbiota transplantation in the treatment of TD have shown promising outcomes [11]. The relationship between intestinal microflora and TD as well as the improvement of TD by improving intestinal microflora is rather a new topic, and larger-scale clinical trials are needed to further confirm the influence of intestinal microflora in TD. Therefore, metabonomics detection of urine and feces is beneficial to further study the pathogenesis of TD.

Metabonomics can detect and analyze patients’ urine, feces and other samples through liquid chromatography-mass spectrometry (LC-MS), and can screen hundreds of metabolites on a large scale [12].Modern scholars have found more than 50 kinds of related biomarkers through metabonomics detection of urine in children with TD [13], including p-hydroxyphenylacetic acid, 1- methylhistidine, 4- pyridoxylic acid, etc., The differential markers mainly involve amino acid metabolism, biosynthesis of unsaturated fatty acid, steroid hormone metabolism and other metabolic pathways.Through the screening of fecal metabonomics [14], some scholars have also proved that Tuina combined with acupuncture stimulation of relevant acupoints can improve the relative abundance of Firmicutes, reduce the relative abundance of Proteobacteria at Phylum level, optimize the structure of intestinal microflora and alleviate or treat symptoms of TD. Our research group conducted preliminary clinical studies and found that there are differences in serum amino acid metabolism between children with brain disorders and healthy children [15]. Therefore, this topic intends to conduct a broad-spectrum screening of urine and feces samples of children with TD by using metabonomics technology to determine their differential metabolites, and then refer to KEGG pathway to explore their possible pathogenesis and provide them with more objective biological indicators.

The medical infrared imaging system (TTM) can detect the specific band of infrared signals of thermal radiation on the body surface, and convert the signal into images that can be distinguished by human vision, reflecting the thermal structure characteristics of the human body [16]. When a certain part/area of the body happened to be experience pathological changes, the part/area around it will first have changes in tissue metabolism that corresponding to certain pathological manifestation which reflected as abnormal temperature of the skin [17].The mediators involved in regulation of body temperature mainly include PGE2, Na+/Ca2+, corticotropin-releasing hormone (CRH), cyclic adenosine monophosphate (cAMP), NO, etc [18]. When there is a change of endogenous substances in the body, these mediators will be affected, reflected as a change in body temperature. Therefore, we hypothesize that children with TD with abnormal metabolites will also experiencing changes in body temperature. In the early stage of our research, we found that indeed there are differences in the structure of the infrared thermography along the governor vessel between healthy children and children with TD. The heat distribution along the governor vessel in healthy children appeared to be in a uniform state (Fig. 1), whereas in children with TD, the heat distribution along the governor vessel shows a tendency of rising/floating (Fig. 2).

**Fig. 1 Fig1:**
[figure not shown]
Temperature distribution in the back region of healthy children. In healthy children, a uniform distribution of heat can be observed in the back region (Fig. 1)

**Fig. 2 Fig2:**
[figure not shown]
Temperature distribution in the back region of TD children. In the back region of TD patients, there is a tendency for heat to rise (Fig. 2)

Combined with the abnormality of metabolic substances in children with TD, we speculate that this metabolic abnormality may be related to the changes of structure of infrared thermography of specific areas along the governor vessel and acupoints around it. Therefore, we aim to investigate the mechanism of acupuncture in regulating the energy metabolism in children with TD, and to further explore the underlying molecular mechanism by which changes of body temperature occur, and to assist in screening out microscopic biomarkers of energy groups related to treatment efficacy, as well as to provide theoretical and experimental basis of infrared thermography technology in diagnosing TD.

Our team’s previous research has confirmed the significant therapeutic effects of acupuncture in relieving symptoms associated with tic disorders in children [19]. Preliminary findings of our studies show that the distribution of infrared thermography along the governor vessel in children with TD have significant changes (Fig. 3). At the same time, we also prove that acupuncture can change the types and contents of serum amino acids in children with encephalopathy [15], and most of these amino acids are involved in energy metabolism [20].

**Fig. 3 Fig3:**
[figure not shown]
Infrared thermographic changes in the back of TD patients. The thermal distribution on the back before and after acupuncture treatment in individuals with TD is presented from left to right

Therefore, we designed this randomized controlled trial to compare the changes of the severity of tic condition before and after the intervention, and to observe the changes of structural characteristic of infrared thermography of body surface/acupoints along the governor vessel and to evaluate the changes of urinary and fecal metabolomics at the end of the treatment. By comparing both the non-intervention group and intervention group, we hope to analyze the relationship between them and to provide further knowledge in understanding the possible mechanism of acupuncture in improving the clinical symptoms of TD via regulating and restoring the body metabolomics network.

## Materials and methods

### Study design and participants

This is a randomized controlled trial, recruiting a total of 90 children (30 healthy children and 60 children with TD) in the outpatient department of acupuncture and rehabilitation department of Affiliated Hospital of Nanjing University of Traditional Chinese Medicine, in which they will be divided into non-intervention group and intervention group. The non-intervention group consists of 30 healthy children while the intervention group consists of 60 children with TD. The intervention group will be randomly allocated into either the treatment group or the control group, with 30 children randomly assigned in each group. Participants with tic disorder will also be recruited through posters and official WeChat accounts. The researchers will use the American Psychiatric Association DSM-5 criteria for tic disorder to assign a diagnosis. Individuals who meet the inclusion criteria will receive free complimentary clinical testing and some treatment subsidies to encourage enrollment. The details of the clinical trial and the collection of samples will be explained to the parents of the patients before obtaining their written consent. This research was approved by the Ethics Committee of the Affiliated Hospital of Nanjing University of Traditional Chinese Medicine (Jiangsu Provincial Hospital of Traditional Chinese Medicine) (2023NL-095-02), and the trial has been registered in China Clinical Trial Registration Center(ChiCTR2300075188).The flow of the trial is presented in Fig. 4. The schedule of the trial is shown in Table 1.

**Fig. 4 Fig4:**
[figure not shown]
Flow chart. Flow chart of the trial

**Table 1 Tab1:** The schedule of the trial

Time point	Study period			
	Baseline		Treatment phase	
	Week − 1	Week 0	Week 1	Week 12
Eligibility Screen	×			
Informed consent	×			
Medical history		×		
Random allocation		×		
Intervention				
Acupuncture group (*n* = 30)			×	×
Sham acupuncture group (*n* = 30)			×	×
Primary outcome	YGTSS	×		×
Secondary outcomes	Urine and feces metabonomics	×		×
	Infrared thermography of du meridian area	×		×
Assessments			×	×
Adverse events			×	×
Comprehensive curative effect evaluation			×	×
Safety evaluation			×	×

### Case criteria

This study commenced in September 2023 and is anticipated to be completed by December 2025. Sixty children diagnosed with tic disorder from the Affiliated Hospital of Nanjing University of Traditional Chinese Medicine will be randomly assigned to either the treatment group or the control group, with 30 children in each group. Additionally, 30 healthy children will be recruited for comparison purposes.

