#### Inclusion criteria

(1) Participants must meet the diagnostic criteria for TD as according to the American Diagnostic and Statistical Manual of Mental Disorders, 5th edition (DSM-5); (2) Age between 3 and 14 years old; (3) Have stopped using other drugs for mental illness for more than 3 months before starting the treatment; (4) Self-volunteer as the subject, signed by the child’s guardian, and children aged 8 and above get their own informed consent.

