### Secondary outcomes

#### Infrared image acquisition at the back along the governor vessel

Infrared images will be captured along the governor vessel of both groups of children: Healthy children and children with TD, aiming to identify any dissimilarities between these two groups. Additionally, infrared images will be captured in children with TD before and after the intervention, as for a comparative analysis.

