#### Metabolomics

Fecal and urine samples will be collected from both groups of children: healthy children and children with TD. Through analysis and detection, biomarkers associated with acupuncture treatment in children with TD can be discovered. Additionally, the KEGG database will be utilized to analyze the metabolic pathways linked to these biomarkers in the acupuncture treatment of children with TD.

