#### Multivariate Statistical Analysis

Preprocessed data will be subjected to unsupervised data analysis using Principal Component Analysis (PCA). A score plot will be used to observe clustering of data from different groups and to remove outlier samples. A loading plot will be utilized to identify components that contribute to inter-group variability, with special attention given to excluding prototype compounds and their metabolites. Additionally, univariate analysis such as fold change (FC) and t-tests will be performed to identify components that exhibit significant statistical differences. Pattern recognition methods, such as Partial Least Squares Discriminant Analysis (PLS-DA) and Orthogonal Partial Least Squares Discriminant Analysis (OPLS-DA), will be employed, and targeted programming and execution using languages such as R or C will be based on the characteristics of the analysis data. Integration of HILIC-TOFMS and RPLC-TOFMS data will be conducted to identify differential components. Multiple methods, including t-tests (*p* < 0.05), FC analysis (FC > 2), and PLS-DA (VIP > 1.5), will be used to screen and confirm potential biomarkers that contribute to inter-group differences, thus identifying potential biomarkers associated with acupuncture treatment in children with TD.

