## Processing of infrared thermographic images

The temperatures of specific acupoints (Dazhui, Zhiyang, Mingmen, Yaoyangguan, and tendon contraction) in the area of the Du meridian will be manually traced. Use SPSS 20.0 statistical software for analysis. Quantitative data is expressed as “mean ± standard deviation” (x ± s). If the data follows a normal distribution, paired sample t-test is used; if the data does not follow a normal distribution, non-parametric tests (Wilcoxon signed-rank test) are used. Skin temperature comparison before and after intervention at different acupoints in different groups is analyzed using one-way analysis of variance (ANOVA) if it follows a normal distribution and has equal variances. If the data follows a normal distribution but has unequal variances, Welch’s test is used. If the data does not follow a normal distribution, Kruskal-Wallis H test is used. *P* < 0.05 indicates statistical significance of the differences.

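### The TD versus healthy comparison is non-randomised, and the article states neither age or sex balance for the healthy children nor an age or sex term in the tests it names

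*Protocol article*

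**What the plan says.** Under Study design and participants the article describes the two populations: "The non-intervention group consists of 30 healthy children while the intervention group consists of 60 children with TD". Case criteria adds only the purpose of the healthy group: "Additionally, 30 healthy children will be recruited for comparison purposes". The Randomization section allocates only the two TD arms.

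The only Inclusion criteria list opens with "Participants must meet the diagnostic criteria for TD" and then sets "Age between 3 and 14 years old". A healthy child cannot meet the first item, so the list does not define the healthy group or its age range.

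Both secondary outcomes use the healthy children. For thermography the contrast is "Healthy children and children with TD, aiming to identify any dissimilarities between these two groups". For metabolomics, "Fecal and urine samples will be collected from both groups of children: healthy children and children with TD".

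On analysis, Multivariate Statistical Analysis says that "univariate analysis such as fold change (FC) and t-tests will be performed to identify components that exhibit significant statistical differences". It then screens candidate markers with p < 0.05, FC > 2 and a PLS-DA VIP above 1.5. Processing of infrared thermographic images has temperatures across groups "analyzed using one-way analysis of variance (ANOVA) if it follows a normal distribution and has equal variances", with Welch or Kruskal-Wallis otherwise. The general Statistical analysis section lists GLM and WLS covariance among its methods, without naming a covariate or the comparison they serve.

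**The concern.** Randomisation makes the two TD arms comparable in expectation. It does nothing for TD against healthy, which is an observational contrast. Ages 3 to 14 run from preschool to adolescence, and it is reasonable to expect metabolite levels and skin temperature to vary with age and sex over that span. If the healthy children happen to be older, younger or differently split by sex, an unadjusted test cannot tell that imbalance from an effect of TD.

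What is at stake is the article's secondary aim: disease-related metabolites and a basis for diagnosing TD by thermography. A marker that in truth tracks age could be carried forward as a marker of TD.

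**Working it through.** **What the plan's own figure covers.** The stated sample size is 30 per randomised arm, from response rates of 95% and 55% and 20% dropout. Power is not stated. At two-sided 5% and 90% power without continuity correction the formula gives 23 per arm, and 23 / (1 − 0.20) = 28.75, so 29, close to 30. The calculation does not involve the healthy group. No figure in the article bears on the TD versus healthy contrast, so what follows is illustration.

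**Inputs from the article.** 60 TD children, 30 healthy children, two-sided tests at 5%.

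**Inputs assumed.** Age SD of 3 years; age gap between groups of 1 to 2 years; correlation r between marker and age of 0.3 to 0.5; no true TD effect. For orientation, ages spread evenly over 3 to 14 would have SD 11 / √12 = 3.2 years.

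**Formulas.** Spurious difference in SD units: d = r × gap / 3. Standard error: √(1/60 + 1/30) = 0.224. Rejection probability: 1 − Φ(1.96 − d/0.224) + Φ(−1.96 − d/0.224).

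| r | gap (years) | d | d / SE | rejection probability |
|---|---|---|---|---|
| 0.3 | 0.5 | 0.05 | 0.22 | 5.6% |
| 0.3 | 1 | 0.10 | 0.45 | 7% |
| 0.4 | 2 | 0.27 | 1.19 | 22% |
| 0.5 | 2 | 0.33 | 1.49 | 32% |

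The first row shows how quickly the problem shrinks when the groups are close in age.

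**Sex, same method.** With an assumed 30-point difference in the share of boys and a sex effect of 0.3, 0.5 or 0.8 SD, the bias is 0.09, 0.15 or 0.24 SD and the rejection probability 6.9%, 10.3% or 18.9%.

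**Metabolites under a joint screen.** Suppose p < 0.05 and FC > 2 must both hold, with fold change taken as a ratio of geometric means, and leave VIP aside. A twofold change is ln 2 = 0.693 on the log scale, or 0.693 / s in SD units for a log-SD of s (assumed). For each s below this exceeds the t-test threshold of 1.96 × 0.224 = 0.44, so fold change decides. At d = 0.267 the pass rate is about 1 − Φ((0.693/s − 0.267) / 0.224); with no imbalance it is 2 × (1 − Φ((0.693/s) / 0.224)).

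| log-SD s | threshold (SD) | pass rate, no imbalance | pass rate, d = 0.267 |
|---|---|---|---|
| 0.7 | 0.99 | below 0.01% | about 0.1% |
| 1.0 | 0.69 | 0.2% | 2.8% |
| 1.3 | 0.53 | 1.7% | 11.7% |

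The joint screen therefore lowers the absolute rate well below 22%, but an age gap still raises it above its value without imbalance.

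**The case against.** - **Silence is not a statement that the groups are unmatched.** A reader might infer that the healthy children will not be matched. The article does not say so. It condenses a fuller protocol, and its supplement and flow chart are not shown. This stands: the accurate wording is that no matching is stated. What remains is that the article goes further than silence on analysis. It names tests and thresholds for these outcomes, and they have no age or sex term.
- **Covariance methods are listed.** It would be too strong to say that the article contains no adjustment. However, GLM covariance appears beside the methods for non-normal data and WLS covariance among those for qualitative data. Neither names a covariate or is linked to the healthy group.
- **The named tests may not be the TD versus healthy tests.** The thermography ANOVA is described for temperatures before and after intervention, while the abstract has healthy children measured at baseline only. Applying it to the healthy contrast is an inference. Likewise, the metabolite screen is said to seek markers associated with acupuncture treatment. Both points stand in part: the outcome sections plan the healthy contrast, and no other test is named for it in the sections on these outcomes.
- **A 22% false-positive rate for metabolites is tempting but unsupported.** It belongs to a lone t-test at assumed values. If the three thresholds apply jointly, which is the natural reading though not explicit, the rate is lower.
- **Later steps do not rescue the contrast.** Confirming a marker against reference standards and correlating it with scale scores do not remove confounding by age.

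**Conclusion.** The point holds for the secondary TD versus healthy contrasts in metabolites and thermography. Followed as written, the plan leaves them open to confounding by age and sex. This rests on what the article states about the healthy group and on the tests it names; for temperature, it also rests on the thermography ANOVA being the test used for this contrast.

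The size is unknown. The range of 7% to 32% applies to a single unadjusted 5% test with 60 against 30, under an assumed 1 to 2 year gap (SD 3) and r of 0.3 to 0.5. It approaches 5% for smaller gaps and is lower for metabolites under joint screening.

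A reader might extend this to the trial's main result. The documents do not support that: acupuncture versus sham is randomised, and YGTSS is not measured in the healthy group. The point is worth acting on because it bears on the biomarker and diagnostic aims and costs little to correct.

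**What to change.** 1. **Analysis.** For each baseline TD versus healthy contrast, replace the unadjusted t-test or ANOVA with a regression of the metabolite (log scale) or acupoint temperature on group, age and sex.
2. **Multivariate screen.** Run PLS-DA and OPLS-DA on features residualised for age and sex, or treat VIP as descriptive for this contrast. Changing the univariate test alone would leave the VIP filter unadjusted.
3. **Recruitment.** State how healthy children are selected. The article reports that recruitment is under way, so matching may be only partly possible. Where healthy recruitment is still open, frequency-match the remaining healthy children to the TD children by age band and sex, and adjust for age and sex in all.

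**Cost.** Slightly slower recruitment of healthy children and a little more analysis work. No additional children are needed, and the randomised comparison does not change. Adjustment after the fact works only as far as the ages of the two groups overlap, so matching is best applied while recruitment continues.
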